### Interventions

#### Treatment group A

The subjects receiving moxibustion treatment will be treated 2 times per week.

During each moxibustion treatment, each acupoint will be treated five times. The moxibustion treatment will last for 25 min. The treatment will continue for 4 weeks. Following the procedures used in several previous studies [11,15,16], acupuncture needles will be inserted bilaterally into three acupuncture points (LI11, ST36, GB39) on the four peripheral extremities and unilaterally into two points (CV4, CV12) in the abdominal region. Indirect moxibustion (Manina, Haitnim Co., Ltd., Korea. 19 mm diameter and 21 mm height) will be used in the trial.

#### Treatment group B

The format will be exactly the same as those for treatment group A, but the subjects receiving moxibustion treatment will be treated three times per week.

### Control group (untreated group)

The control group (untreated group) will receive no treatment. The subject in this group will be asked to maintain their normal lifestyle, including diet, exercise and workload.

### Permitted and prohibited concomitant treatments

Brochures containing information on dietary changes, living habits, and exercise regimens that help prevent and alleviate hypertension will be distributed to all groups, and the subjects will decide for themselves whether to incorporate the suggested changes into their daily lives.

All groups will be prohibited from undergoing active treatment to lower the blood pressure for the duration of their participation in this clinical trial. After the completion of the clinical trial, during the assessment period, the subjects will be allowed to decide for themselves whether to receive additional treatment. Any other related information will be recorded in detail.

The use of birth control pills and central nervous system stimulants or depressants, which can affect blood pressure, will remain prohibited. The practitioner will be allowed to converse with the subjects about daily care and treatment details while carrying out the required examination.

### Outcome measures

The primary outcome measurement in this study is the change in blood pressure before randomization (baseline) and 4 weeks after randomization. Blood pressure will be taken at every visit.

The secondary outcome measures will be the mean pulse pressure, body mass index (BMI), heart rate variability (HRV), the Modified Stress Response Inventory (SRI-MF), the Pittsburgh Sleep Quality Index (PSQI), the Fatigue Severity Scale (FSS), EuroQol (EQ-5D), general assessments and blood tests including fasting blood sugar (FBS), uric acid, lipid profile, high sensitivity C-reactive protein (hs-CRP), liver function test (LFT), hemoglobin A1c (HbA1C), and complete blood count (CBC).

The pulse pressure refers to the difference between the systolic pressure and the diastolic pressure. This value reflects the degree of stiffness of the blood vessels. An increase in the pulse pressure after midlife is recognized as a risk factor for cardiovascular diseases [17]. The BMI will be calculated, and laboratory tests including FBS, uric acid, lipid profile, LFT, HbA1C, and CBC will be performed before and after treatment. The subjects will fast for 12 h before blood is drawn for these tests. hs-CRP is an index used to assess the degree of risk for cardiovascular diseases and to determine prognosis [18]. After 10 min of relaxation, the HRV will be measured with electrodes attached to both wrists and ankles using QECG-3 (LXC3203, Laxtha Inc., Korea) to obtain the LF/HF ratio, TP, VLF, LF, HF, heart rate, SDNN, RMSSD, HRV index, and PNN50. The neck disability index (NDI) consists of ten questions: seven about whether the subject is able to perform functional activities, two about symptoms, and one about concentration [19]. The EQ-5D is a questionnaire that is used to assess the quality of life [20]. The subjects mark the best answers for five questions on mobility, self-care, pain, usual activities, and psychological status. The answers are given in the form of numbers (1 = no problem, 2 = moderate problem, 3 = severe problem), and the sum of the five numbers reflects the subject’s health status. Global assessments of the patients will be used to assess improvement following the treatment, as judged by the subjects [21]. The subjects can choose from five answers for questions on the degree of improvement or worsening of the blood pressure: “improved a lot,” “somewhat improved,” “no change,” “somewhat worsened,” and “worsened a lot.” The SRI-MF consists of 22 questions that are related to somatization (9 items), depression (9 items), and anger (3 items) [22]. The subjects will mark the best answer for each of the questions based on their experience in the past week. The assessment is performed by adding up the scores of each item to obtain a total score. The PSQI was used to assess the quality of sleep and to identify sleep disorders [23]. The PSQI is an index used to assess the quality of sleep and the presence of any sleep disorders in the past month. This questionnaire assesses seven items: subjective quality of sleep, latency, sleep duration, habitual sleep efficiency, factors that disturb sleep, use of sleeping aids, and impediments to daytime functioning. The FSS is a questionnaire consisting of nine items that is used to investigate the severity of fatigue during the past week [24,25]. A Pattern Identification questionnaire was developed specifically to determine whether there are differences in the distributions of the change in symptoms among the groups (Table 2).

**Table 2 T2:** Content of baseline and follow-up questionnaires

**Measures**	**Baseline**	**End of treatment**	**Follow-up**
		**at 4 weeks after randomization**	**at 8, 12, 16, 20 and 24 weeks after randomization**
Informed consent	x	-	-
Inclusion/exclusion criteria	x	-	-
Randomization	x	-	-
Demographic information taking	x	-	-
Blood pressure	x	x	x
Blood test	x	x	-
General assessment	-	x	-
BMI (body mass index)	x	x	x
NDI (neck disability index)	x	x	x
EQ-5D (EuroQol)	x	x	x
PSQI (Pittsburgh Sleep Quality Index)	x	x	x
HRV (heart rate variability)	x	x	x
Questionnaire of pattern identification	x	x	x
SRI-MF (modified form of the Stress Response Inventory)	x	x	x
FSS (Fatigue Severity Scale)	x	x	x
Adverse events	-	x	x

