**Methods/design:**

Forty-five subjects with pre- or stage I hypertension will be randomized into three groups: treatment group A (2 times/week), treatment group B (3 times/week), and the control group (non-treated group). The inclusion criteria will be as follows: (1) aged between 19 and 65 years; (2) prehypertension or stage I hypertension (JNC 7, Seventh Report of the Joint National Committee on the Prevention, Detection, Evaluation, and Treatment of High Blood Pressure); (3) the participants are volunteers and written consent obtained.

The participants in the treatment group A will undergo indirect moxibustion 2 times per week for 4 weeks, and the participants in the treatment group B will undergo indirect moxibustion 3 times per week for 4 weeks. The participants in the control group (non-treated group) will maintain their current lifestyle, including diet and exercise. The use of antihypertensive medication is not permitted. The primary endpoint will be a change in patient blood pressure. The secondary endpoints will be the body mass index, lipid profile, EuroQol and Heart Rate Variability. The data will be analyzed with the Student’s t-test and analysis of variance (ANOVA) (*p* < 0.05).

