### Statistical analysis

The results of the intention-to-treat (ITT) analysis will be used to assess the validity of the study as a whole. The per-protocol (PP) analysis results will be used as a reference. The ITT analysis will be used as the main safety assessment technique.

Continuous data will be represented by the average, standard deviation, minimum value, and maximum value, whereas categorical data will be represented by a frequency table. For the comparison of the results among the groups, the analysis of variance (ANOVA) test will be used when the data are normally distributed; the Kruskal-Wallis test will be used otherwise. In addition, the chi-square test will be performed for categorical data.

After 4 weeks, the differences in systolic and diastolic pressure will be summarized for each group using descriptive statistics, including the median, average, standard deviation, and interquartile range. In addition, we will evaluate the effectiveness of the treatment using an analysis of covariance as the dependent variable, the baseline score as the covariate, the group as the fixed factor, and the hypertension stage as the stratified variable. In addition, we will compare the results for the stratified groups with the results for the whole subject pool (non-stratified) to determine whether hypertension stage is a suitable stratification variable. The differences in the systolic pressure and diastolic pressure following the treatment for each group will be analyzed using a paired t-test or a Wilcoxon signed rank test, and the 95% confidence interval will be presented. To assess the difference in the tendency for each visit, repeated measures analysis of variance will be performed. A significance level of 5% will be used in all analyses.

The average pulse pressure, change in the baseline blood pressure following the treatment, BMI, EQ-5D, Ankle Brachial Pressure Index(ABI index), Brachial-Ankle Pulse wave velocity(PWV index), heart rate variation (LF/HF ratio, TP, VLF, LF, HF, heart rate, SDNN, LF norm, HF norm), and blood test results will be analyzed using the same techniques used to analyze the validity of the assessment variable. To determine whether there are differences in the distribution of the change in symptoms among the groups, analysis will be performed on each item using the chi-squared test.

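### EQ-5D is scored as an unweighted sum of five ordinal codes, so unlike health states share a score, and the rank tests the article offers for some comparisons do not undo that

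*Protocol article*

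**What the plan says.** The Outcome measures section of the protocol article describes the EQ-5D as "five questions on mobility, self-care, pain, usual activities, and psychological status". Answers are coded "1 = no problem, 2 = moderate problem, 3 = severe problem". The scoring rule follows directly: "the sum of the five numbers reflects the subject"'s health status. No weights or index are mentioned, and the direction of the score is not stated.

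The abstract gives the instrument a visible role: "The secondary endpoints will be the body mass index, lipid profile, EuroQol and Heart Rate Variability". Table 2 schedules it at baseline, at week 4 and at the five follow-up visits.

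The Statistical analysis section lists it with pulse pressure, heart rate variability and blood tests ("change in the baseline blood pressure following the treatment, BMI, EQ-5D") and says that these variables "will be analyzed using the same techniques used to analyze the validity of the assessment variable". Read in context, those techniques are the ones set out for blood pressure:

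- ANCOVA, with "the baseline score as the covariate, the group as the fixed factor"
- a paired t-test or Wilcoxon signed rank test within each group
- repeated measures ANOVA over visits
- as the general group comparison, ANOVA, or Kruskal-Wallis if the data are not normal

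**The concern.** The codes 1, 2 and 3 are labels for ordered categories. Adding them brings in two assumptions that the article does not argue for: that moving from none to moderate is worth the same as moving from moderate to severe, and that a step in pain is worth the same as a step in self-care or mobility.

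If either assumption fails, a group difference of, say, one point on the sum has no fixed meaning as quality of life. A participant can also move between clearly different states and show no change at all. The trial is a pilot whose stated aims include testing its methods, so a scoring rule fixed here could be carried into the larger trial.

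**Working it through.** The article states no numerical figure for EQ-5D, so there is none to reproduce. The check is an enumeration under the article's own coding.

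**Inputs** (all from Outcome measures): five items, three levels each, codes 1, 2, 3, score = plain sum.

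**Range and number of profiles.** Minimum 5 × 1 = 5, maximum 5 × 3 = 15, so 11 possible scores. Number of profiles: 3^5 = 243.

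**Profiles per score:**

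| Score | 5 | 6 | 7 | 8 | 9 | 10 | 11 | 12 | 13 | 14 | 15 |
|---|---|---|---|---|---|---|---|---|---|---|---|
| Profiles | 1 | 5 | 15 | 30 | 45 | 51 | 45 | 30 | 15 | 5 | 1 |

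Only scores 5 and 15 identify a single profile.

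**What shares a score** (levels sorted within profile):

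- Score 7: 1+1+1+1+3 (5 profiles) and 1+1+1+2+2 (10 profiles).
- Score 8: 1+1+1+2+3 (20) and 1+1+2+2+2 (10).
- Score 9: 1+1+1+3+3 (10), 1+1+2+2+3 (30) and 1+2+2+2+2 (5).
- Score 10: 1+1+2+3+3 (30), 1+2+2+2+3 (20) and 2+2+2+2+2 (1).

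**Profiles with a severe problem.** Profiles with no code 3 number 2^5 = 32, so 243 − 32 = 211 contain at least one severe problem. Scores 7 to 10 mix the two kinds: 15 + 30 + 45 + 51 = 141 profiles, of which 10 + 10 + 5 + 1 = 26 have no severe problem. So 141 − 26 = 115 of the 211 profiles with a severe problem share their sum with a profile that has none.

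**Dependence on the coding.** Keep none = 1 and moderate = 2, and write s for the severe code. One severe problem with four unaffected dimensions scores 4 + s; two moderate problems with three unaffected dimensions score 3 + 4 = 7. The two are equal only when s = 3. With s above 3 the first is worse, and with s between 2 and 3 the second is worse. Every such choice respects the order none < moderate < severe, so it is the equal spacing that makes these two states tie.

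**Do the rank options help?** Kruskal-Wallis and Wilcoxon remove the normality assumption, but they rank the sums. Two profiles that both score 7 enter as tied values, and a participant who moves from one to the other has a paired difference of zero. ANCOVA and repeated measures ANOVA use the sum as an interval quantity and have no alternative named.

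**Is there a dimension-level analysis elsewhere?** The item-by-item chi-squared test in Statistical analysis is for the distribution of change in symptoms. Outcome measures ties that purpose to the Pattern Identification questionnaire, not to EQ-5D.

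**The case against.** Several points on the other side are fair.

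- **Rank methods are named.** It would be wrong to say that the sum goes only into parametric tests. This stands as a limit on the criticism of the tests, but not of the score.
- **The link is across two sections.** Statistical analysis lists EQ-5D without saying that the analysed variable is the sum, and a fuller protocol might add an index. However, the sum is the only EQ-5D score the article defines. That is a stated rule, not a detail left out, and analysing the sum is its natural reading.
- **The participants may be fairly healthy.** They are aged 19 to 65, take no blood-pressure medication and have no history of major disease. A reader might infer from the enumeration that most patients will be misclassified, for example because scores 9 to 11 cover 45 + 51 + 45 = 141 of 243 profiles (58%). The article does not support that: it gives no EQ-5D distribution, and the count treats all profiles alike. If scores cluster at 5 and 6, ties between severe and non-severe states do not arise, because score 6 is always a single moderate problem. The ambiguity starts at 7.
- **Any single number hides some change.** Opposite movements in two dimensions can offset in a weighted index as well, so cancellation is no special fault of the sum.
- **The instrument's cited reference is not at hand.** One cannot say that no support for summing exists, only that the article gives none.
- **The role is modest.** The full list of secondary outcomes is much longer than the four in the abstract, and no sample size or decision is tied to EQ-5D.

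**Conclusion.** The point holds as a minor improvement. The article fixes an EQ-5D score that assumes equal steps and equal dimensions, and that score ties unlike states from 7 upwards. The rank tests offered for some comparisons do not repair this.

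By the article's own coding, 243 profiles reduce to 11 scores, and 115 of the 211 profiles with a severe problem share a sum with one that has none. These figures describe the scoring rule. How often such ties would occur in 45 participants cannot be derived from the document.

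The conclusion rests on one reading: that the EQ-5D variable analysed is the sum defined in Outcome measures. It does not extend to the trial's main result. The primary blood-pressure outcome is unaffected, and the individual answers are collected, so rescoring remains possible.

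**What to change.** - **Dimensions.** Report the five dimensions separately by group as ordered categories, compared with a rank test. This alone removes the core problem and needs no external weights.
- **Summary score.** Replace the sum in the outcome definition with a preference-weighted index, using one value set named and cited before analysis. The article mentions no value set, so the choice is the sponsor's.
- **If the sum is kept.** Label it an unweighted descriptive score and state that higher means worse health.

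The cost is a line or two in the outcome definition and a scoring step on answers already collected. The downsides are that a value set must be chosen and justified, and that five comparisons per analysed visit are reported where one stood before, so they should be presented as descriptive or exploratory.

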### Follow-up

Follow-up tests will be conducted at 8, 12, 16, 20 and 24 weeks after randomization. The follow-up assessment is designed to evaluate the long-term effects of moxibustion.

### Statistical analysis

The results of the intention-to-treat (ITT) analysis will be used to assess the validity of the study as a whole. The per-protocol (PP) analysis results will be used as a reference. The ITT analysis will be used as the main safety assessment technique.

Continuous data will be represented by the average, standard deviation, minimum value, and maximum value, whereas categorical data will be represented by a frequency table. For the comparison of the results among the groups, the analysis of variance (ANOVA) test will be used when the data are normally distributed; the Kruskal-Wallis test will be used otherwise. In addition, the chi-square test will be performed for categorical data.

After 4 weeks, the differences in systolic and diastolic pressure will be summarized for each group using descriptive statistics, including the median, average, standard deviation, and interquartile range. In addition, we will evaluate the effectiveness of the treatment using an analysis of covariance as the dependent variable, the baseline score as the covariate, the group as the fixed factor, and the hypertension stage as the stratified variable. In addition, we will compare the results for the stratified groups with the results for the whole subject pool (non-stratified) to determine whether hypertension stage is a suitable stratification variable. The differences in the systolic pressure and diastolic pressure following the treatment for each group will be analyzed using a paired t-test or a Wilcoxon signed rank test, and the 95% confidence interval will be presented. To assess the difference in the tendency for each visit, repeated measures analysis of variance will be performed. A significance level of 5% will be used in all analyses.

The average pulse pressure, change in the baseline blood pressure following the treatment, BMI, EQ-5D, Ankle Brachial Pressure Index(ABI index), Brachial-Ankle Pulse wave velocity(PWV index), heart rate variation (LF/HF ratio, TP, VLF, LF, HF, heart rate, SDNN, LF norm, HF norm), and blood test results will be analyzed using the same techniques used to analyze the validity of the assessment variable. To determine whether there are differences in the distribution of the change in symptoms among the groups, analysis will be performed on each item using the chi-squared test.

All adverse reactions manifested will be listed with detailed explanations. The frequency of abnormal reactions that are correlated with the treatment and abnormal reactions that do not have such correlations will be recorded. A Fisher’s exact test will be performed to determine whether there are any differences among the groups with respect to the incidence of abnormal reactions as reported by the subjects. Furthermore, technical analysis will be performed to identify differences in the degree of severity and in the type of abnormal reactions among the groups.

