### Design

This study will be a prospective randomized controlled trial, and participants will be recruited from Woo-suk University Hospital using notices at the hospital and newspaper advertisements.

In this pilot clinical trial, patients with pre- or stage I hypertension will be analyzed to determine the safety and efficacy of moxibustion, and basic analysis will be performed on the results. The study participants will voluntarily sign clinical trial consent forms, and all examinations and tests will be performed according to the clinical trial plan. Eligible subjects will be chosen based on specific inclusion and exclusion criteria. Participants will be randomized before the first treatment. Forty-five subjects with pre- or stage I hypertension will be randomized into three groups: treatment group A (2 times/week), treatment group B (3 times/week), and the control group (non-treated group). During each moxibustion treatment, each acupoint will be treated five times. The treatment will continue for 4 weeks. The follow-up assessment is designed to evaluate the long-term effects of moxibustion. Upon completion of the 4-week-long treatment, follow-up tests will be conducted at weeks 8,12,16,20 and 24 after randomization (Figure 1).

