### Randomization

This study is designed as a pilot study to calculate the appropriate sample size for future randomized clinical trials. Allowing for a 20% dropout rate, each group will include 15 participants, which is the minimum sample size necessary to evaluate the effect of moxibustion [13,14]. In this study, stratified randomization will be performed by classifying subjects into age and sex by an online centralized randomization service.

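### The main safety analysis is by intention to treat, so any group A or B participant who never has a moxibustion session would lower the reported reaction rate; the follow-up safety window also needs fixing

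*Protocol article*

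**What the plan says.** The Statistical analysis section of the protocol article makes intention to treat the lead analysis for harms: "The ITT analysis will be used as the main safety assessment technique". The only other analysis set named is the per-protocol set, with a minor role: "The per-protocol (PP) analysis results will be used as a reference". No set based on exposure is named.

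Five other places bear on this point:

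- Design, on timing: "Participants will be randomized before the first treatment".
- Randomization, on numbers: "Allowing for a 20% dropout rate, each group will include 15 participants".
- Control group: "The control group (untreated group) will receive no treatment".
- Permitted and prohibited concomitant treatments, on the assessment period: "the subjects will be allowed to decide for themselves whether to receive additional treatment". The sentence excepts no group and does not say what the additional treatment may be.
- Table 2, whose columns are baseline, week 4 and weeks 8 to 24: "Adverse events - x x". Events are therefore marked at follow-up as well as at the end of treatment.

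The Adverse events section names the expected harms as local skin reactions, requires no causal link for an event to count, and says that events during treatment will be recorded. The end of the Statistical analysis section plans a Fisher's exact test of reaction incidence among the groups. It also records reactions related and unrelated to treatment separately.

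**The concern.** Analysis by assignment protects an efficacy comparison, but it is not the cautious choice for a harm caused by exposure. A participant who never has a session cannot be burned by moxibustion. Counting that person in the denominator makes the reaction rate look lower than it is among people treated. The Design section makes safety one of the purposes of this pilot, and with 15 per group a single person matters.

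A second issue lies beside the first. If the by-group comparison runs to week 24, it covers a period in which anyone may have started another treatment. Reactions to that treatment would be counted under the randomized group. This comes from the choice of time window, not from intention to treat as such, and needs its own remedy.

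**Working it through.** **The plan's own figure.** The article gives no expected reaction rate, so the only figure to reproduce is the group size. Twelve completers (back-calculated, not stated) inflated for 20% dropout give 12 / (1 − 0.20) = 15 per group, and 3 × 15 = 45. This agrees with the plan. The dropout allowance is 0.20 × 15 = 3 per group.

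**Dilution of the rate.** Let r be the reaction rate among exposed participants and k the number of the 15 who never have a session. Then

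intention-to-treat rate = r × (15 − k) / 15.

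The article gives neither r nor k, so both are assumed. The range for k is 0 to 3, where 3 means that the entire dropout allowance leaves before session 1.

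| k | factor | r = 25% | r = 33.3% | r = 50% |
|---|---|---|---|---|
| 0 | 1.00 | 25.0% | 33.3% | 50.0% |
| 1 | 0.93 | 23.3% | 31.1% | 46.7% |
| 2 | 0.87 | 21.7% | 28.9% | 43.3% |
| 3 | 0.80 | 20.0% | 26.7% | 40.0% |

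**Effect on the planned test.** The plan compares the three groups, so I used the exact three-group Fisher test (full enumeration with margins fixed, summing all tables no more probable than the one observed). Assume 4 reactions in A, 4 in B and none in 15 controls:

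- all 15 counted in A and in B: p = 0.097
- one unexposed removed from each of A and B (14, 14, 15): p = 0.062
- two removed from each (13, 13, 15): p = 0.038
- three removed from each (12, 12, 15): p = 0.0235

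For one active group against control (two-sided), 4/15 against 0/15 gives p = 0.100, 4/14 gives p = 0.042 and 4/12 gives p = 0.028. These counts are chosen for illustration. They show that results near the 5% level can turn on one or two people, not that they will.

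**The follow-up window.** Take 5, 5 and 0 reactions in groups of 15, for which the three-group p = 0.030. Now add one reaction to some later treatment:

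- in a control (5, 5, 1): p = 0.170
- in group A (6, 5, 0): p = 0.0225

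The first narrows the contrast and the second widens it. The article allows either, so no net direction can be claimed.

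**The two statements on the window.** The Adverse events text refers to events during treatment, that is, the 4-week course. Table 2 marks adverse events at weeks 8, 12, 16, 20 and 24 as well. The article does not say which period the by-group test covers.

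**The case against.** The case against has real force.

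- **No one is said to go untreated.** The 20% dropout is not tied to leaving before the first session, and people who leave part-way have been exposed and belong in any safety set. A reader might infer that the plan's rates will be diluted by a fifth. The article does not support that: 0.80 is the far end of an assumed range, and at k = 0 nothing is lost.
- **Intention to treat is not defined in the article.** The full protocol may already require one session. Nothing shown says so, but if it does, the denominator problem is already solved.
- **Later treatment need not hide harm.** A reader might infer that follow-up events will be charged to the controls and so mask a moxibustion effect. But all groups may take additional treatment, and it need not be moxibustion. Groups A and B could gain events too.
- **Safeguards exist.** Reactions are to be listed, dated and judged for relation to treatment, and outside drugs noted. With 45 participants a careful reader could trace most late events. This softens the problem but does not remove it: the stated test is still by group and on the reactions that subjects report.
- **Randomization has value for harms too.** Dropping unexposed A and B participants while keeping every control departs from the randomized comparison. This is a reason to keep intention to treat as a supportive display, not to make it the lead.

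**Conclusion.** The concern holds in a conditional form. The article fixes intention to treat as the main safety analysis in a trial where randomization precedes exposure and the expected harms require exposure. Any A or B participant without a session can only lower the reported rate, by a factor of 0.93 for one of 15 and 0.80 for an assumed worst case of three; the effect is nil if there are none. This rests on intention to treat meaning everyone randomized, and on a background rate of these skin reactions near zero without moxibustion.

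The follow-up matter is separate. Comparing groups over all 24 weeks mixes in reactions to unspecified later treatments, with no known direction, and the text and Table 2 disagree on the period that counts. This reads the assessment period in the concomitant-treatment section as the follow-up after week 4. If only events in the 4-week course enter the comparison, this part largely falls away.

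Both parts merit a correction because it is cheap, not because a large bias has been shown.

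**What to change.** Replace the sentence on the main safety analysis with wording to this effect: the main safety set comprises all controls and all group A and B participants who received at least one moxibustion session, analysed in the group to which they were randomized. An A or B participant with no session is listed separately. Keeping A and B as randomized matters because the two differ only in frequency. Regrouping by sessions attended could move people between them and spoil the frequency comparison that the Discussion promises.

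Then:

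- name weeks 0 to 4 as the window for the by-group safety comparison;
- list events from week 4 to week 24 separately, each flagged by any treatment started in that period;
- reconcile the Adverse events text with Table 2 on when events are recorded;
- keep the intention-to-treat tabulation as supportive.

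The cost is small. Reaction dates are already to be recorded, and the concomitant-treatment section provides for recording related information in detail. The article does not say that session attendance is recorded, so who had at least one session must be captured. Reported reaction rates may become slightly less favourable.

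### PSQI, FSS, SRI-MF, NDI and three HRV indices are measured at baseline and week 4 but are left off the list of outcomes given the baseline-adjusted analysis

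*Protocol article*

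**What the plan says.** All of this is in the protocol article.

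- **Outcome measures.** The secondary outcomes include "the Modified Stress Response Inventory (SRI-MF), the Pittsburgh Sleep Quality Index (PSQI), the Fatigue Severity Scale (FSS), EuroQol (EQ-5D") among others. The same section describes the NDI, and it names RMSSD, HRV index and PNN50 among the quantities taken from the HRV recording.
- **Table 2.** PSQI, FSS, SRI-MF, NDI, HRV and EQ-5D share one schedule: baseline, week 4 and every follow-up.
- **Statistical analysis, general rule.** "For the comparison of the results among the groups, the analysis of variance (ANOVA) test will be used when the data are normally distributed"; Kruskal-Wallis is used otherwise. The sentence names no outcome, has no covariate, and does not say whether the response is the week-4 value or the change.
- **Statistical analysis, blood pressure paragraph.** This adds an ANCOVA with the baseline score as covariate, group as fixed factor and hypertension stage as stratifying variable. The sentence omits its dependent variable. A repeated measures ANOVA follows in the same paragraph.
- **Statistical analysis, last paragraph on efficacy.** Pulse pressure, blood pressure change, BMI, EQ-5D, ABI, PWV, nine named HRV quantities and "blood test results will be analyzed using the same techniques used to analyze the validity of the assessment variable". PSQI, FSS, SRI-MF, NDI, RMSSD, PNN50 and HRV index are not in it.
- **Level and size.** "A significance level of 5% will be used in all analyses". "Forty-five subjects with pre- or stage I hypertension will be randomized into three groups". "Allowing for a 20% dropout rate, each group will include 15 participants".

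**The concern.** Four questionnaires other than EQ-5D are collected on exactly the EQ-5D schedule, yet only EQ-5D is assigned the method that uses its baseline value. No reason is given. Three HRV indices are likewise separated from the rest of the same recording.

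With 15 or fewer per arm, and randomization stratified by age and sex rather than by these scores, chance differences in baseline sleep, fatigue or stress can be appreciable. A comparison of week-4 scores carries such a difference into the estimate. A comparison of change scores over-corrects for it when the baseline to week-4 correlation is below 1, which is regression to the mean. Either way the error variance is larger than it needs to be, although the baseline values that would reduce it are already being collected.

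**Working it through.** **Step 1: which outcomes are covered.**

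| Outcome | Baseline and week 4 in Table 2 | On the list analysed like blood pressure |
|---|---|---|
| EQ-5D, BMI | yes | yes |
| PSQI, FSS, SRI-MF | yes | no |
| NDI | yes | no |
| RMSSD, PNN50, HRV index | yes (under HRV) | no |
| ABI, PWV | not in Table 2 or Outcome measures | yes |

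The list and the schedule disagree in both directions.

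**Step 2: inputs.**
- From the article: three groups, 15 per group, 5% level, 20% dropout.
- Derived: 15 × (1 − 0.20) = 12 completers per group. The article does not state the 12. It gives no effect size, SD or power, so there is no power figure of its own to reproduce.
- Assumed, because the article gives neither: a standardized difference d from control, and a correlation r between baseline and week-4 score, with equal SDs at both times (set to 1).

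**Step 3: formulas.** Error variance V:
- ANOVA on week-4 score: V = 1, error df = 3n − 3
- ANOVA on change: V = 2(1 − r), error df = 3n − 3
- ANCOVA: V = 1 − r², error df = 3n − 4

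With group means (0, d, d), the squared deviations from the grand mean sum to 2d²/3. The noncentrality is λ = n(2d²/3)/V, and power is the probability that a noncentral F with 2 and the error df exceeds its 5% critical value.

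**Step 4: main case, n = 12 and d = 0.8.** Here 12 × 2 × 0.64/3 = 5.12, so λ = 5.12/V. The critical values are 3.285 (33 df) and 3.295 (32 df).

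| r | Week-4: λ, power | Change: λ, power | ANCOVA: λ, power | Gain over week-4 | Gain over change |
|---|---|---|---|---|---|
| 0.3 | 5.12, 47.6% | 3.66, 35.4% | 5.63, 51.4% | 3.8 | 16.0 |
| 0.5 | 5.12, 47.6% | 5.12, 47.6% | 6.83, 60.0% | 12.4 | 12.4 |
| 0.7 | 5.12, 47.6% | 8.53, 70.5% | 10.04, 77.7% | 30.1 | 7.2 |

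At r = 0.5, V falls from 1 to 0.75, a 25% cut in error variance against either form of ANOVA.

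**Step 5: sensitivity.**
- 15 per group, d = 0.8, r = 0.5: 58.1% to 71.3%, a gain of 13.3 points (from unrounded powers).
- Means (0, d/2, d), n = 12, d = 0.8, r = 0.5: 37.0% to 47.5%, a gain of 10.5 points.
- n = 12, d = 0.5, means (0, d, d), against week-4 scores: gains of 1.7, 5.8 and 16.7 points at r = 0.3, 0.5 and 0.7.
- Over both mean patterns, both group sizes, d from 0.3 to 1.2 and r from 0.3 to 0.8: about 0.4 to 44 points against week-4 scores and about 0 to 20 against change. ANCOVA was never the less powerful choice in the scenarios computed.

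**The case against.** The strongest reply is that this is silence in a condensed article. No sentence says that these scores will be analysed without baseline, the list contains no word such as only, and models for individual secondary scales can be left to a fuller document. This has some force but does not dispose of the point. The article goes down to single HRV quantities in assigning methods, and it separates EQ-5D from questionnaires on the same schedule. That is an allocation, and a fuller plan that copied it would carry the gap forward.

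A reader might infer that these outcomes get only an unadjusted test. The text does not settle that. The ANOVA sentence does not fix its response, and if the response is change, baseline is partly used. The ANCOVA sentence lacks its dependent variable, and the repeated measures sentence names no outcome; their place in the blood pressure paragraph favours the narrow reading without proving it.

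A reader might also quote a loss of 12 points as a property of the design. It is one cell of the table above, resting on a d and an r that the article does not supply.

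A further reading is that the sample size of the future trial would be distorted. This is weak. Blood pressure is the primary outcome and already has ANCOVA, and an adjusted SD can be computed later for any scale because both values are collected.

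It is also true that randomization keeps the comparison without the covariate valid, and that a pilot without a power target breaks no stated design aim by losing power on secondary scales.

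**Conclusion.** The point holds in a limited form. Seven measures with baseline values are left off the list that receives baseline adjustment, and the only between-group rule that clearly reaches them is ANOVA or Kruskal-Wallis without a baseline covariate.

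The cost is precision. Under the assumed 0.8 SD difference in both treated arms and 12 per arm, it is about 4 to 30 points of power if week-4 scores are compared, and about 16 down to 7 points if changes are compared, as the correlation goes from 0.3 to 0.7. With smaller effects and weak correlation it is close to nil. No invalid inference is at issue, and the consequence is modest. The case for changing the text is that a better analysis is available from data already collected. The mismatch with ABI and PWV also suggests that the list was not reconciled with the outcomes, rather than chosen deliberately.

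**What to change.** In the Statistical analysis section, add PSQI, FSS, SRI-MF, NDI, RMSSD, PNN50 and HRV index to the outcomes analysed like blood pressure. State the model in full: week-4 value as dependent variable, the same outcome's baseline value as covariate, group as factor. Name this as the reported between-group comparison. Supplying the dependent variable also repairs the incomplete ANCOVA sentence.

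Then reconcile the analysis list with the Outcome measures section and Table 2. ABI and PWV should either be added to both or removed from the list.

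For the seven added measures the cost is a sentence or two of text and one degree of freedom per model for the covariate. It needs no new data, visits or participants. If ABI and PWV are kept, their measurement has to be scheduled.
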